### Outcomes and adverse events

The primary endpoint for Intervention A is overall exposure to antibiotics in the PCT and pyuria guidance group compared to the control group. Endpoints are assessed at discharge from hospital, and 30 and 90 days after admission. As secondary endpoints, we will compare the PCT-pyuria group with the control group regarding:

A. Clinical and microbiological cure 7 days after end of therapy.

B. 30-day rate of clinical and microbiological recurrence.

C. 90-day rate of clinical and microbiological recurrence.

D. Antibiotic-associated side effects.

Regardless of group assignment, we will investigate:

E. The relationships of pyuria, urine culture cutoffs and urinary α1-microglobulin/creatinine ratio with the presence of pyelonephritis and level of biomarkers (CRP, PCT, ProADM, and other biomarkers such as urea, natriuretic peptides (ANP, BNP), copeptin, endothelin, apoprotein A1).

F. Correlation between sonographic signs of pyelonephritis and diagnosis based on urine culture cutoffs, clinical criteria and biomarkers.

Our hypothesis for the secondary endpoints A to C is that there is no difference between the two study groups. Our hypothesis for endpoints E and F is that urinary markers and contrast-enhanced ultrasound correlate with systemic biomarkers and diagnosis of pyelonephritis.

For the primary endpoint for Intervention B, we assess the length of physician-led hospitalization in the ProADM-guided triage group compared to the control group within a follow-up of 90 days. As secondary endpoints, we will compare the ProADM group with the control group regarding:

A. resource utilization, defined as the length of index hospitalization (physician- and/or nurse-led); rate and length of re-hospitalization; rate of general practitioner visits; rate of medical investigations and interventions related to UTI and overall, rate of treatment changes related to UTI, for example, antibiotic escalations. The hypothesis is that there are no excess re-hospitalizations or visits to the GP while there are fewer treatment changes and medical investigations in the ProADM group.

B. Proportion of patients triaged according to the risk assessment bundles. The hypothesis is that physician adherence to site-of-care decisions will be 20% higher in the intervention group.

C. Functional status (defined by SPI, activities of daily living and instrumental activities of daily living) and adverse events (that is the recurrence rate at 30 days, rate of complications (acute renal failure, ICU requirement, nosocomial infections or medication side effects), delirium, falls or pressure ulcers). Our hypothesis is that there is no difference in the functional status achieved 30 days after inclusion between the two groups.

D. Patient satisfaction with the provided service and quality of care at 30 days and 90 days.

E. Healthcare-related quality of life at the day of discharge as measured with the EQ-5D questionnaire. The hypothesis for D and E is that there is no difference in patient satisfaction and health-related quality of life between the intervention and the control groups.

F. We will describe the effective and chargeable costs for the entire treatment pathway in an exploratory economic analysis.

Endpoints will be assessed at hospital discharge, and 30 and 90 days after admission. An adverse event in a subject is defined as any untoward occurrence of any unfavorable and unintended clinically relevant medical sign, any symptom or any disease temporally associated with the study, which must not necessarily have a causal relationship with the study procedure. Any serious unexpected adverse event (for example, transfer to ICU, re-hospitalization, recurrence of an UTI, papillary necrosis, intrarenal or perirenal abscess, emphysematous pyelonephritis, allergic reaction to contrast medium during ultrasound or death) within 180 days after study inclusion is monitored by the data safety and monitoring board (DSMB). All adverse events will be followed until resolution, until the condition stabilizes, until the event is otherwise explained or the subject is lost to follow-up.

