## Methods

This is a randomized controlled open-label trial using a two-by-two factorial study design with two independent internet-based 1:1 randomizations (one each for the antibiotic part and one for the triage part, respectively) (Figure 1). The objectives are first, for Intervention A, to analyze the efficacy and safety of a PCT- and pyuria-guided antibiotic therapy in individualizing and reducing the duration of antibiotic treatment compared to the guidelines [4,10,19,37] and second, for Intervention B, to test the impact on LOS of ProADM-enhanced triage decisions compared to standard care. Both interventions are for a high-intensity implementation of interdisciplinary risk assessment for triage in patients with UTIs presenting to an ED. LOS is defined as the number of days of physician-led hospitalization until discharge to ambulatory or nurse-led care.

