#### Intervention A

Appropriate antibiotics and minimal duration of antibiotic treatment are based on recent guidelines [10] after local adaptation by a panel of experts. PCT is used to guide antibiotic treatment (Figure 2). We use fosfomycin (3 g single dose) [40] and trimethoprim-sulfamethoxazole (800/160 mg twice daily) for simple UTIs. Furthermore we use ciprofloxacin orally (500 mg twice daily or 250 mg twice daily if the estimated glomerular filtration rate <30 ml/min/1.73 m2) or ceftriaxone intravenously (2 g daily) for febrile UTIs/pyelonephritis. If known, previous antibiotic resistant profiles are considered. If there is a non-susceptible urine pathogen in the current urine culture the antibiotic therapy is adjusted. In inpatients, antibiotic duration is based on absolute values of PCT and relative decreases of PCT levels and pyuria. In outpatients, the antibiotic duration is based on absolute values of PCT only. PCT and pyuria are measured on admission, and, in hospitalized patients, every other day as long as the patient receives antibiotics for the UTI. Pyuria criteria are derived from local data on female patients with UTIs [15]. PCT cutoffs are derived from data from our recent observational study and after extrapolation from patients with LRTIs and sepsis [36,41,42]. Patients with uncomplicated simple UTIs in the PCT group receive NSAIDs regardless of PCT values for symptom resolution given emerging data [43,44]. In the control group, antibiotic durations are recommended based on guidelines (Figure 2).

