#### Measurements

Urine sediment analysis, urine culture with an antibiotic resistance profile and urinary protein profile (α1-microglobulin/creatinine ratio) are performed on admission. In patients with a diagnosis of febrile UTI/pyelonephritis, blood cultures are taken prior to administration of antibiotics. These patients also receive an ultrasound evaluation of the urinary tract, including Doppler examination as well as a CEUS examination of both kidneys.

Chargeable and effective costs will be gathered from the finance and controlling departments to calculate costs per patient from study entry until discharge to a non-hospital setting. Data on outcome and complications will be collected by the study team.

All patients are called by members of the study team (who are unaware of the randomization group) on days 30 and 90 after randomization to inquire about clinical recurrences, antibiotic side effects and the preparedness for discharge [52] using a questionnaire with a ten-point Likert scale response format. Interviews are standardized according to a protocol and interviewers receive formal introductory training.

Physicians in this trial know that their behavior is monitored. Since it is not feasible to have ProADM and PCT values blinded in the control groups, however, algorithm compliance is reinforced according to assigned groups by the study team.

Both contrast-enhanced ultrasound criteria and urinary protein profiles are used together with urine and clinical criteria and biomarker levels for the final classification as upper or lower UTI. For final analysis, culture confirmation will be required (Table 1).

**Table 1 T1:** Urine culture cutoffs for significance

**Diagnosis**	**Criteria**
Uncomplicated, simple UTI	≥10^3^ cfu/ml
Uncomplicated febrile UTI/pyelonephritis	≥10^4^ cfu/ml
Complicated UTI (simple or febrile UTI/pyelonephritis)	
in women	≥10^5^ cfu/ml
in men	≥10^4^ cfu/ml
in straight catheter urine	≥10^4^ cfu/ml

cfu: colony-forming unit; UTI: urinary tract infection.

Healthcare-related quality of life on the day of discharge is measured with the EQ-5D questionnaire. EQ-5D includes the 15-item EQ-5D self-classifier, which assesses the health-related quality of life among five dimensions and the EQVas, which obtains a self-rating of the current health-related quality of life [53].

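### Intervention A's only side-effect endpoint and the follow-up calls cover antibiotics alone, although the PCT arm also directs NSAIDs, and complications other than recurrence have no stated comparison by PCT arm

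*Protocol article*

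**What the plan says.** In Methods, the objective of Intervention A is "to analyze the efficacy and safety of a PCT- and pyuria-guided antibiotic therapy", with the aim of individualizing and shortening treatment.

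Outcomes and adverse events gives four secondary endpoints to be compared between the PCT-pyuria group and control:

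- Cure, listed as "A. Clinical and microbiological cure 7 days after end of therapy"
- Early recurrence, listed as "B. 30-day rate of clinical and microbiological recurrence"
- Later recurrence, listed as item C, which repeats item B at 90 days
- Side effects, listed as "D. Antibiotic-associated side effects"

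Items E and F of that list are analysed regardless of group. A no-difference hypothesis is stated for A to C and none for D.

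Under Intervention A, the protocol states: "Patients with uncomplicated simple UTIs in the PCT group receive NSAIDs regardless of PCT values for symptom resolution given emerging data". Under Measurements, callers unaware of allocation telephone all patients on days 30 and 90 "to inquire about clinical recurrences, antibiotic side effects and the preparedness for discharge".

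The broader harm endpoints stand in the list for ProADM versus control. Its item A includes re-hospitalization. Its item C includes 30-day recurrence and the "rate of complications (acute renal failure, ICU requirement, nosocomial infections or medication side effects), delirium, falls or pressure ulcers". The same section defines adverse events widely and has the DSMB monitor serious unexpected events for 180 days. Those events include ICU transfer, re-hospitalization, recurrence, the named renal complications and death.

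**The concern.** The two factors have harm endpoints of different breadth, and the breadth does not match what each factor does. Intervention A decides on drugs, yet its side-effect endpoint covers one drug class. Intervention B decides on site of care, yet its list covers side effects of medication generally.

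A strategy that shortens antibiotic treatment would be expected to lower antibiotic side effects, and that is a genuine benefit. The difficulty is that endpoint D has no place for a harm that could offset it, including harm from a drug the PCT arm itself directs. The complications that might follow from too little antibiotic, recurrence apart, are not named as outcomes of the factor that changes antibiotic duration. A report that followed these lists could present a favourable side-effect result for PCT guidance without the figures needed to weigh it.

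**Working it through.** **Step 1. Set the harms beside the comparisons stated for them.**

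| Harm | Compared by PCT arm | Compared by ProADM arm | Other mention |
|---|---|---|---|
| Lack of cure | Yes (A) | No | |
| Recurrence | Yes (B, C: 30 and 90 days) | Yes (C: 30 days) | Also a DSMB-monitored serious event |
| Antibiotic side effects | Yes (D) | Within medication side effects | Day 30/90 calls |
| NSAID side effects | No | Within medication side effects | General adverse-event definition |
| Acute renal failure | No | Yes (C) | Overruling criterion for prolonged antibiotics |
| ICU need | No | Yes (C) | DSMB; overruling criterion for prolonged antibiotics |
| Re-hospitalization | No | Yes (A) | DSMB |
| Abscess, papillary necrosis, emphysematous pyelonephritis | No | Not named | DSMB; overruling criteria for prolonged antibiotics |
| Death | No | Not named | DSMB |

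The section on overruling criteria makes ICU admission, acute renal failure and the three renal complications grounds for prolonged antibiotic therapy. The protocol therefore already treats them as relevant to antibiotic duration. A comparison by ProADM arm does not replace one by PCT arm: the randomizations are independent, so the ProADM contrast averages over PCT allocation.

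**Step 2. The plan's own figures.** The sample size for Intervention A assumes 8 versus 10 days with SD 5. With two-sided 5% alpha and 80% power, n = 2 × (1.960 + 0.842)² × 5² / 2² ≈ 98.1, which rounds up to the stated 99 per arm. The point does not depend on this figure, but it supplies the ratio 8/10 = 0.8 used next.

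**Step 3. How endpoint D moves with exposure (assumed rates).** If side-effect risk were proportional to antibiotic days, control rates of 10%, 20% and 30% would give 8%, 16% and 24% in the PCT arm. The differences are 2, 4 and 6 percentage points. On that assumption they are true reductions, but nothing is set against them.

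**Step 4. What endpoint D leaves out (assumed rates).** Let a share s of the PCT arm take NSAIDs only, with side-effect rate a on antibiotics and r on NSAIDs, and let controls have no NSAID harm.

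- Difference on D: s × a
- Difference on all medication: s × (a − r)
- Left out by D: s × r

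With s = 15%, a = 15% and r = 10%, D reads 15.0% versus 0.85 × 15% = 12.75%. All medication reads 15.0% versus 12.75% + 1.5% = 14.25%. D omits 1.5 of the 2.25 points. With s from 5% to 25% and r = 10%, it omits 0.5 to 2.5 points. The share omitted is r/a whatever the value of s: two thirds here, one third if r were 5%. It reflects the assumed rates and says nothing specific about this trial.

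**Step 5. What the added comparisons could show.** With 250 enrolled and 20% lost, 200 remain, or 100 per arm; without loss there are 125. For equal event rates p, the 95% half-width is 1.96 × √(2p(1 − p)/n).

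| Assumed control rate | Half-width, 100 / 125 per arm (points) | Power to detect a doubling, 100 / 125 per arm |
|---|---|---|
| 2% | ±3.9 / ±3.5 | 13% / 15% |
| 5% | ±6.0 / ±5.4 | 27% / 32% |
| 10% | ±8.3 / ±7.4 | 51% / 60% |

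These comparisons can describe, but not establish equivalence.

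**The case against.** Three of the four between-arm secondary endpoints for Intervention A are cure and recurrence. They are direct outcomes of under-treatment and can count against the arm given fewer antibiotics. The protocol itself names recurrence as a serious event. This stands: a reader might infer that PCT guidance has no safety comparison beyond D, or that serious events are compared only across the ProADM arms, and neither is so.

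The adverse-event definition requires no causal link and is not limited to any arm, so an NSAID harm falls within it. A reader might infer that such harms go unrecorded, but the article does not say that. What is missing is a stated comparison by PCT arm and a routine question after discharge. The full protocol or SAP may add tables by both factors, which independent randomization makes valid. Tables cannot, however, recover answers to a question that the calls did not ask, and the published call content names antibiotics only.

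Finally, the article says that these patients receive NSAIDs, not that antibiotics are withheld from them. The figure with the algorithm is not shown, and nothing is said about NSAID use in controls. This stands against any numerical claim about the size of the distortion. It does not affect the finding that NSAID harm lies outside D.

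**Conclusion.** The concern holds in limited form. As written, the side-effect contrast for Intervention A is one-sided: it counts antibiotic side effects, leaves out those of a drug the PCT arm directs, and has no stated companion comparison for complications other than recurrence, or for death. With cure and recurrence in place, the plan supports the safety objective of Intervention A in part. To say that it cannot support that objective at all would go too far.

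The size of the effect cannot be computed from the article. The illustrations rest on assumed side-effect rates, an assumed NSAID-only share and no NSAID harm in controls. The finding about the endpoint lists and the call content needs none of these assumptions.

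**What to change.** - Reword endpoint D of Intervention A as side effects of any medication given for the UTI, antibiotics or NSAIDs. Antibiotic side effects can remain as a component.
- Put the same question, in the same words, to all patients in both arms in the blinded day 30 and 90 calls.
- Report re-hospitalization, ICU transfer, acute renal failure, the renal complications already on the DSMB list, and death by both randomized factors. Give estimates with confidence intervals and label them descriptive. This fits the section on analysis of secondary endpoints, which disclaims power for non-inferiority and promises effect sizes with intervals.

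The cost is changed endpoint wording, one broader question in existing calls and one further set of tables. No patients or visits are added and no treatment rule changes. The downside is a few more low-power secondary comparisons and a possibly less favourable side-effect contrast for the PCT arm.

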### Sample size

#### Intervention A

The first co-primary objective is to show that the duration of antibiotic therapy in the index hospitalization is 2 days shorter in the PCT group (8 days, standard deviation ±5) than in the control group (10 days, standard deviation ±5). These estimates are based on a historical control group in our hospital [31,36]. According to these estimations, 99 patients per arm would provide an 80% power at the 5% alpha level.

#### Intervention B

Similarly, for LOS estimation in patients with UTI we used data from a previous study performed on site at the Cantonal Hospital of Aarau during 2011, which approximated 6 days (standard deviation ±4) [36]. Our working hypothesis is that index hospitalization is 1.5 days shorter in the ProADM group (4.5 days, standard deviation ±4). According to these estimations, 112 patients per arm would provide an 80% power at the 5% alpha level (total sample size 224).

Based on previous research at the Cantonal Hospital of Aarau, there will be approximately 180 to 200 patients with UTI in a 12-month period, of which approximately 75 are expected to consent to this trial. Thus we estimate to complete the trial within 36 months.

The necessary sample sizes are shown in Table 2 assuming varying differences in LOS and antibiotic duration between the two intervention groups. Therefore, we will aim for a sample size of 250.

**Table 2 T2:** Sample size considerations

**Time 1**	**Time 2**	**Power**	**Alpha-level**	**SD**	**Number per group**
10	8	0.8	0.05	4	63
10	8	0.8	0.05	5	99
10	8	0.8	0.05	6	142
10	9	0.8	0.05	4	252
10	9	0.8	0.05	5	393
10	9	0.8	0.05	6	566
6	4.5	0.8	0.05	4	112
6	4.5	0.8	0.05	5	175
6	4.5	0.8	0.05	6	252
6	5	0.8	0.05	4	252
6	5	0.8	0.05	5	393
6	5	0.8	0.05	6	566

### Statistical considerations

The primary analysis population will be the full analysis set, which includes all patients following an intention-to-treat principle. Every effort will be made to keep the number of losses to follow-up minimal. A sensitivity analysis will be carried out including only patients with evaluable primary endpoint data to assess potential bias due to patients lost to follow-up. Two co-primary endpoints will be used to compare, for Intervention A, the duration of antibiotic therapy and, for Intervention B, the length of physician-led hospitalization. A secondary analysis population, the per-protocol population, will be defined, which excludes major protocol violators. Specifically, patients will be excluded from the per-protocol population if they fulfill any of the following: violation of inclusion or exclusion criteria, not treated according to the trial requirements (that is, overriding of triage recommendations on admission or on day 3 without a pre-specified reason) or lost to follow-up. As a sensitivity analysis, the primary analysis will be repeated on the subset of patients with evaluable outcomes (that is, drop-outs are excluded from this additional analysis) and repeated on the per-protocol population.

To test the two continuous primary endpoints of this two-by-two factorial design study we will use the Mann–Whitney *U* test and calculate a median regression model [54]. We do not expect an interaction between the co-primary endpoints (for Intervention A the duration of antibiotic therapy and for intervention B the length of stay in our study). In our previous studies we showed that the shorter duration of antibiotic therapy in LRTIs did not influence the overall length of stay [41,55]. However, our algorithm for antibiotic guidance is different between inpatients and outpatients, which makes effect modification possible. Therefore we will formally test for an interaction using the median regression model. We are aware that the test for an interaction may result in a false negative due to the low power and the rather small sample size [56,57].

In a second step, the primary endpoint will be explored for association with potential prognostic factors in a median regression model considering potential confounding factors such as: age, sex, UTI subgroup, time to reach stability, co-morbidities, patient preferences and living conditions prior to hospitalization.

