**Methods and design:**

This randomized controlled open-label trial has a factorial design (2 × 2). Randomization of patients will be based on a pre-specified computer-generated randomization list and independent for the two interventions. Adults with UTI presenting to the emergency department (ED) will be screened and enrolled after providing informed consent.

For our first Intervention (A), we developed a protocol based on previous observational research to recommend initiation and duration of antibiotic use based on the clinical presentation of UTI, pyuria and PCT levels. For our second intervention (B), an algorithm was developed to support site-of care decisions based on the prognostic marker ProADM and distinct nursing factors on days 1 and 3. Both interventions will be compared with a control group conforming to the guidelines.

The primary endpoints for the two interventions will be: (A) overall exposure to antibiotics and (B) length of physician-led hospitalization within a follow-up of 30 days. Endpoints are assessed at discharge from hospital, and 30 and 90 days after admission. We plan to screen 300 patients and enroll 250 for an anticipated estimated loss of follow-up of 20%. This will provide adequate power for the two interventions.

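### The sensitivity analyses meant to assess bias from loss to follow-up all leave out the lost patients, so their agreement with the primary result would not rule out outcome-dependent loss

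*Protocol article*

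**What the plan says.** The abstract (Methods and design) sets the scale: "We plan to screen 300 patients and enroll 250 for an anticipated estimated loss of follow-up of 20" per cent. Statistical considerations then defines the main population: "The primary analysis population will be the full analysis set, which includes all patients following an intention-to-treat principle". The article does not say how a patient without a primary outcome enters that set.

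The same paragraph names one analysis for the loss problem, "including only patients with evaluable primary endpoint data to assess potential bias due to patients lost to follow-up". It restates it a few sentences later with the gloss that "drop-outs are excluded from this additional analysis", and adds a repeat in the per-protocol population. The exclusions from that population end with "overriding of triage recommendations on admission or on day 3 without a pre-specified reason) or lost to follow-up", so it omits the lost patients as well.

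For the co-primary endpoints, "we will use the Mann–Whitney *U* test and calculate a median regression model". Both methods need an outcome value, observed or imputed, for every patient analysed.

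**The concern.** Whether loss to follow-up biases the comparison depends on how the unseen outcomes differ from the seen ones, and whether that difference varies by arm. An analysis restricted to patients with outcomes holds the same blind spot. Here the article itself picks the method and gives it this purpose, so the point is about a stated choice and not about detail left to a fuller plan.

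What can be missing is time after discharge. For Intervention A this is antibiotic days taken at home, by outpatients and by patients discharged on treatment. For Intervention B it is later physician-led hospital days, if the 30-day window (abstract) or the 90-day window (Outcomes and adverse events) is what counts. The trial is open-label and both interventions aim to change time on antibiotics or in hospital, so loss that differs by arm is plausible. The risk is that two similar results are reported as evidence that loss did no harm.

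**Working it through.** **1. The two possible readings of the primary analysis**

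- *No imputation.* Mann–Whitney and median regression then use only patients with outcomes. The evaluable-outcome analysis uses the same patients and returns the same result.
- *Some rule fills in the missing outcome.* The two analyses can then differ, but the gap measures the effect of that rule. It does not measure the outcome-dependent part of the loss, and a gap near zero does not show that part to be small.

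The per-protocol repeat adds nothing on this question, because it excludes the same patients. No analysis described in the article varies the assumption about unseen outcomes.

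**2. Inputs and the plan's own figures**

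From Sample size: A, 8 days in the PCT group, fewer "than in the control group (10 days, standard deviation ±5" days), so a difference of 2 and SD 5; B, 6 versus 4.5 days, difference 1.5, SD 4; 80% power, 5% alpha (two-sided reproduces the figures).

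n per arm = 2 × (1.96 + 0.842)² × SD² / difference²
- A: 98.1, rounded up to 99, as stated.
- B: 111.6, rounded up to 112, as stated.

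**3. How large an excess among the lost would matter**

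Assumptions: 250 enrolled, so 125 per arm for each factor; 20% of primary outcomes missing in each arm, leaving 100 evaluable; the planned effect is seen in the evaluable patients; lost controls resemble observed controls; normal approximation for means. An excess of x days among lost intervention patients reduces the all-patient difference by 0.2x.

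SE = SD × √(2/100); tipping excess = (difference − 1.96 × SE) / 0.2

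| | SE | 1.96 × SE | Tipping excess |
|---|---|---|---|
| B | 0.566 | 1.109 | (1.5 − 1.109)/0.2 = 1.96 days |
| A | 0.707 | 1.386 | (2 − 1.386)/0.2 = 3.07 days |

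With the SE taken on all 125 per arm (0.506 and 0.632), the same formula gives 2.5 days (B) and 3.8 days (A).

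With 10% missing, 112.5 are evaluable per arm:
- B: SE 0.533, (1.5 − 1.045)/0.1 = 4.5 days.
- A: SE 0.667, (2 − 1.307)/0.1 = 6.9 days.

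**4. False positives if there is no true effect**

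A 3-day excess among the lost in one arm, at 20% missing, biases the complete-case difference by 0.2 × 3 = 0.6 days. In SE units this is 0.6/0.566 = 1.06 (B) and 0.6/0.707 = 0.85 (A). A nominal 5% two-sided z-test then rejects with probability about 18.5% (B) and 13.6% (A).

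**5. Does the planned comparison give a warning?**

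Simulation: 4,000 trials, 125 per arm, no true effect on length of stay, mean 6, SD 4. One arm loses 35% of patients staying above 6 days and 5% of the rest (20% overall); the other loses 20% at random.

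- Normal outcomes, missing values filled with the observed arm mean: complete-case bias 0.61 days, Mann–Whitney rejection on complete cases 21%. The filled-in all-patient analysis shows the same 0.61 days, so there is no gap and no warning. The arm-mean rule guarantees this match.
- Gamma-distributed outcomes, each lost patient keeping the recorded index stay, no later hospital days: complete-case bias about 0.56 days with 19% rejection; all-patient bias 0.00 with 4.8% rejection. Here the gap does expose the problem.
- As the previous case, but with 10% of patients re-hospitalised for a mean of 6 days (assumed): biases of 0.66 and 0.12 days, rejection 21% and 6%.

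The value of the comparison therefore turns on a handling rule that the article does not state.

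**The case against.** A reader might infer that the complete-case analysis cannot detect the bias at all and carries no information about it. The article does not support that. Its full analysis set is said to contain all patients, so the evaluable-outcome analysis is one half of a comparison. Under some rules, such as keeping recorded index-stay days, the comparison is informative, as step 5 shows. The rule itself may stand in a fuller plan.

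A second tempting reading is that 20% of primary outcomes will be missing. The 20% is overall loss, in a trial with calls at days 30 and 90. The opening of Methods counts length of stay up to discharge, Sample size frames both targets around the index hospitalization, and length of re-hospitalization is a separate secondary endpoint. On that reading Intervention B's outcome is largely in hospital records. This objection stands: 20% is an upper bound. Some missingness remains, more for A than for B, because antibiotic days at home need follow-up and because the 30- and 90-day windows are also stated.

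Third, the tipping figures come from a z-test on means with a shift in one arm only. Under Mann–Whitney or median regression, shifting a fifth of the patients does not move the estimate by a fifth of the shift. This also stands, and the figures are illustrative.

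None of this makes the described set of analyses adequate. Where the comparison does help, the help comes from the unstated handling rule, and agreement still leaves outcome-dependent loss open.

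**Conclusion.** The point holds in a limited form. The analyses offered against loss-to-follow-up bias exclude the lost patients, and none varies the assumption about their outcomes. They are poorly suited to the stated purpose, without being uninformative under every handling rule.

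At the upper bound of 20% missing, an excess of about 2.0 days (B) or 3.1 days (A) among lost intervention patients would remove significance from the planned effects. At 10% missing the figures are about 4.5 and 6.9 days. They rest on the planning SDs, a normal approximation for means, and a loss effect confined to one arm. They show that the question deserves a proper analysis; they do not predict bias in this trial. The change is worth making because it is cheap.

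**What to change.** Keep the evaluable-outcome analysis as a descriptive line and remove its role as the assessment of loss-to-follow-up bias. In its place specify:

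- Multiple imputation by arm under missing at random, using baseline and recorded index-stay data. Recorded days are kept, and only unobserved post-discharge days are imputed.
- A delta-adjusted tipping-point analysis that adds 0 to 5 days to the imputed intervention-arm values and reports the shift at which the conclusion changes.

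Run both with the planned Mann–Whitney test and median regression, and state how results are combined across imputations. At low missingness the conclusion may hold over the whole 0-to-5-day range, and the report should then say so.

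The cost is a little extra programming and analysis. No new data or patients are needed.
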